As described in following sections, intention-to-treat analyses will be performed for both primary endpoints. Where necessary, e.g., in the event of cluster withdrawal, as-treated and/or per-protocol analyses will be performed as secondary analyses.

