### Randomized allocation of the intervention

Randomization was conducted in February 2022. Eight out of 15 clusters were randomly selected to receive male *Wolbachia-Aedes* deployments and the rest designated non-intervention clusters. Due to the small number of clusters available for randomization, selection of clusters relied on a constrained randomization strategy to prevent chance imbalances in baseline characteristics between intervention and non-intervention clusters. The proportion of positive to negative dengue samples was used as the constraining variable. A large number of potential random cluster allocations in 8:7 intervention/non-intervention ratio were generated (*n* = 10,000).

For each allocation, the value of the constraining variable was calculated in each study arm using the aggregate arm-level value. Each potential random allocation was evaluated against the pre-defined balancing criteria (i.e., no statistically significant difference in the proportion of positive to negative dengue samples between the two arms) and removed as a potential random allocation if they were not met. All potential allocations that satisfy the balancing criteria were kept (*n* = 3151, exceeding the threshold of 100–150 allocations recommended in the literature), and a single allocation was randomly selected from within the restricted list of balanced allocations. Finally, a single random draw was used to determine which of the two study arms was to receive male *Wolbachia-Aedes* releases. Randomization will be followed by extensive community engagement to seek the support of local politicians and grassroot leaders of each of the eight intervention clusters.

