### Statistical analysis: primary endpoint—impact of male *Wolbachia-Aedes* deployments on dengue incidence, measured by laboratory-confirmed reported dengue case counts normalized by population size in intervention versus non-intervention clusters

We will monitor trends in reported laboratory-confirmed dengue case counts in intervention and non-intervention clusters, before, during, and after male *Wolbachia-Aedes* deployments take place. We aim to use a quasi-experimental approach to examine the impact of male *Wolbachia-Aedes* deployment on routine dengue case notifications normalized by cluster population size. Namely, we will use regression models to model the monthly, normalized dengue case counts across sites; we will control for population size and seasonal variability through weather station observations and autocorrelation between sites by inclusion of lag terms. To estimate the impact of male *Wolbachia-Aedes* deployments on routine dengue case counts, the regression specification will include a binary group variable to denote whether a cluster is an intervention/non-intervention cluster, and a binary treatment variable denoted 1 will be included to indicate when interventions occur within that cluster [55]. Following similar difference-in-difference strategies [56], the interaction term between the group and treatment variables will then yield a coefficient, which provides an estimate of the intervention effect of male *Wolbachia-Aedes* deployments on monthly reported case counts. This approach ensures that extraneous factors and selection bias, such as level changes in dengue case counts in either intervention/non-intervention arms post-intervention are removed [56]. Should pre-trends assumptions in dengue case counts between intervention/non-intervention clusters be violated under this quasi-experimental approach, we will instead use synthetic control methods which can more appropriately identify the impact of male *Wolbachia-Aedes* deployments on routine dengue case notifications.

In both primary endpoints, intention-to-treat analysis will classify all individuals/clusters respectively allocated to the intervention arm in the randomization stage as such, notwithstanding any non-treatment of the intervention clusters. In per-protocol analysis, any dropouts of the intervention clusters will be removed from the analysis, and only intervention clusters receiving intervention treatment as well as the allocated controls will be analyzed.

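### The secondary per-protocol analysis drops withdrawn intervention clusters but keeps all seven controls, so its test-negative odds ratio is exposed to selection bias if withdrawal is related to dengue risk (minor)

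*Protocol article*

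**What the plan says.** The protocol article ranks its analysis sets clearly. Under Study design, "intention-to-treat analyses will be performed for both primary endpoints", and "in the event of cluster withdrawal, as-treated and/or per-protocol analyses will be performed as secondary analyses". The last paragraph of the statistical analysis section for the case-count endpoint covers both primary endpoints. Under intention-to-treat, clusters stay in their allocated arm "notwithstanding any non-treatment of the intervention clusters". Under per-protocol, "any dropouts of the intervention clusters will be removed from the analysis, and only intervention clusters receiving intervention treatment" are kept, together with every cluster allocated to the control arm. No exclusion rule is given for the non-intervention clusters.

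Randomized allocation of the intervention gives the route by which a cluster might drop out: "Randomization will be followed by extensive community engagement to seek the support of local politicians and grassroot leaders of each of the eight intervention clusters". The same section says that the allocation was drawn from those showing no significant arm difference in the proportion of positive to negative dengue samples, evaluated over the full 8:7 set.

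**The concern.** A non-intervention cluster is asked for nothing, and the survey section describes these clusters as having no community engagement. A cluster whose leaders would have refused therefore stays in the comparison if it was allocated to control, and leaves if it was allocated to intervention. The retained intervention clusters are then a selected subset set against an unselected control arm.

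Constrained randomisation was adopted because there are only 15 clusters, and each intervention cluster is one-eighth of its arm. The balance was achieved for the full set and need not survive the loss of one or two clusters. As described, the model for the test-negative endpoint is a logistic regression on arm of residence with no baseline term, so nothing in it would restore comparability. The per-protocol odds ratio could then depart from 1 without any intervention effect, and a reader may take it as efficacy when the releases are actually delivered.

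**Working it through.** The plan gives no figure for this analysis, so there is nothing to reproduce. The question is how far one-sided deletion can move the odds ratio when the true value is 1.

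**Inputs from the protocol article:** 8 intervention and 7 non-intervention clusters; withdrawn intervention clusters deleted; all controls kept.

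**Assumptions (not in the document):** between-cluster SD of log dengue odds 0.3 to 0.5; one or two clusters withdraw; cluster effects are normal; clusters are weighted equally, as an approximation to the aggregate odds ratio.

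**Worst case, the highest-risk clusters leave.** The expected largest of 8 standard normal draws is about 1.424, and the expected sum of the two largest is about 2.276. The eight draws have expected sum zero, so the mean of those remaining is:

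- one removed: −1.424 / 7 = −0.203 SD
- two removed: −2.276 / 6 = −0.379 SD

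The controls have mean zero, so the apparent ratio is exp(mean × SD):

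| Removed | SD 0.3 | SD 0.5 |
|---|---|---|
| 1 of 8 | exp(−0.061) = 0.94 | exp(−0.102) = 0.90 |
| 2 of 8 | exp(−0.114) = 0.89 | exp(−0.190) = 0.83 |

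This is an apparent reduction of 6% to 17%. If the lowest-risk clusters leave, the log shift is the same size with the opposite sign: ratios of about 1.06 to 1.11 for one cluster and 1.12 to 1.21 for two.

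**Less extreme withdrawal.** A simulation with 200,000 replicates, no true effect and a wider set of assumed SDs gave these per-protocol ratios:

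| Relation of withdrawal to risk | Removed | SD 0.2 | SD 0.4 | SD 0.6 |
|---|---|---|---|---|
| None | 1 or 2 | 1.00 | 1.00 | 1.00 |
| Correlation 0.5 | 1 | 0.98 | 0.96 | 0.94 |
| Correlation 0.5 | 2 | 0.96 | 0.93 | 0.89 |
| Highest risk leave | 1 | 0.96 | 0.92 | 0.89 |
| Highest risk leave | 2 | 0.93 | 0.86 | 0.80 |

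The intention-to-treat ratio was 1.00 throughout.

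**Second primary endpoint.** These ratios come from differences in baseline level. The difference-in-differences model removes stable level differences between the retained clusters and the controls, so the figures do not carry over. Selection matters there only if withdrawal is related to the trend in incidence.

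**The case against.** The strongest reply is that this is what per-protocol means: units that did not receive the allocated intervention are left out, and control clusters that would have refused cannot be seen. The analysis is secondary and may never be run. That stands, and it is why the point concerns how a supportive result is built and read. It is not an error or a contradiction in the plan.

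The shifts are also modest beside cluster-level noise. At SD 0.3, the log shift of −0.061 compares with a standard error of about 0.3 × √(1/7 + 1/7) = 0.16 under simple randomisation, and −0.114 with about 0.3 × √(1/6 + 1/7) = 0.17. That stands too, although noise is reflected in an interval that allows for clustering and a systematic shift is not.

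Three stronger readings are tempting and are not supported:

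- A reader might infer that the per-protocol comparison is biased. Bias needs a withdrawal and a link between withdrawal and dengue risk. The document reports neither, and the direction would be unknown.
- A reader might infer that the trial's main conclusion is at risk. Intention-to-treat governs both primary endpoints and keeps every allocated cluster.
- A reader might infer that many valid treated months will be lost. The rule most naturally reads as removing the whole cluster, but the text does not address withdrawal part-way through. Table 1 puts community engagement from June 2022 and releases from July 2022, so an early refusal would forfeit few treated months or none.

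Nor does the document say in words that only intervention clusters can withdraw. That is the only route it describes.

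**Conclusion.** The concern holds in limited form, with minor severity. The stated rule removes clusters from one arm after randomisation and can undo the constrained balance, so the per-protocol odds ratio for the test-negative endpoint is exposed to selection bias of unknown direction. Under no effect, the worst case is roughly 6% to 10% for one cluster and 11% to 17% for two. It shrinks under partial correlation and vanishes if withdrawal is unrelated to risk. These sizes rest on assumed SDs and withdrawal counts, since the document gives neither.

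The rule is also stricter than it needs to be. Outcomes come from the laboratory surveillance network, so data for a withdrawn cluster remain available, and the second endpoint's model already carries an indicator for when interventions occur within a cluster.

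**What to change.** Amend the per-protocol paragraph as follows, before any withdrawal is known:

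1. Keep a withdrawn cluster's treated months and censor it from its withdrawal month instead of deleting it.
2. Adjust the per-protocol model for the test-negative endpoint for each cluster's historical test positivity. The trial already holds this as its constraining variable.
3. Report baseline dengue measures of withdrawn and retained intervention clusters side by side.
4. Label the per-protocol result supportive and non-randomised.

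The cost is a wording change and a small analysis on data already collected. One cluster-level covariate with 15 clusters will widen the interval slightly. Censoring makes follow-up uneven over calendar time between the arms, so the censored model should allow for calendar period. A cluster that never receives releases contributes no treated months under either rule, so there only steps 2 to 4 help. Some selection may remain after adjustment, which is why the label matters. An instrumental-variable estimate that keeps all 15 clusters is an option, but it would be imprecise and bring further assumptions, so it need not be required.

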### Statistical analysis: secondary endpoint—impact of male *Wolbachia-Aedes* deployments on the prevalence of *Ae. aegypti/Ae. albopictus* mosquitoes

Similarly, we will test whether male *Wolbachia-Aedes* deployments will effectively suppress *Ae. aegypti* mosquito populations as well as whether they have spillover impact on *Ae. albopictus* mosquito populations. Using the nationally representative network of Gravitraps as described above, we will employ a similar quasi-experimental approach to examine the impact of male *Wolbachia-Aedes* deployment on routinely collected *Ae. aegypti/Ae. albopictus* mosquito population data. Namely, we will use regression models with the normal link to model the mean weekly captured *Ae. aegypti/Ae. albopictus* per trap across clusters and control for seasonal variability through weather station observations and autocorrelation between clusters by inclusion of lagged mosquito population terms. To estimate the impact of male *Wolbachia-Aedes* deployments on *Ae. aegypti/Ae. albopictus* mosquito populations, the regression specification will include a binary group treatment variable to denote whether a site is an intervention/non-intervention cluster, and a binary treatment variable denoted 1 will be included to indicate when interventions occur within that cluster [55]. Following other difference-in-difference strategies [56], the intervention term between the group and treatment variables will then yield a coefficient, which provides an estimate of the intervention effect of *Wolbachia-Aedes* interventions on *Ae. aegypti/Ae. albopictus* mosquito populations weekly. This approach ensures that extraneous factors and selection bias, such as level changes in *Ae. aegypti/Ae. albopictus* mosquito populations in either intervention/non-intervention arms post-intervention are removed. Should pre-trends assumptions in *Ae. aegypti/Ae. albopictus* mosquito populations between intervention/non-intervention clusters be violated under this quasi-experimental approach, we will instead use synthetic control methods which can more appropriately identify the impact of male *Wolbachia-Aedes* deployment on the dependent variable of interest.

### Statistical analysis: secondary endpoint—impact of male *Wolbachia-Aedes* deployments on community attitudes/knowledge and acceptance

Using prospectively collected household survey data as described in preceding sections, we will test for differences in engagement and awareness across engagement arms in male *Wolbachia-Aedes* deployment clusters, across 3 sentiment surveys, after which differences and changes in residents’ knowledge attitudes and perceptions on male *Wolbachia-Aedes* deployment and vector control practices will be evaluated across intervention and engagement arms. Responses from all survey waves across intervention/non-intervention sites will first be hypothesis tested for differences in the captured socio-demographic characteristics. If there are between-wave differences in socio-demographic characteristics, propensity score matching will be conducted and/or synthetic weights assigned to each observation to mirror the national level socio-demographic composition. To examine the impact of the trial on community endpoints, logistic/multinomial regressions with site- and trial-specific fixed effects will be used, with socio-demographic controls added. An interaction term between site and trial indicator variables will be added to test overall outcome differences over time between intervention and non-intervention clusters and across engagement arms. Additionally, comparisons across engagement arms will be conducted to determine efficacies of engagement strategies. These analyses will then yield coefficients which allow computation of the odds and marginal odds ratios for each corresponding factor on the community attitude/knowledge/acceptance outcome measure referenced from baseline. Lastly, differences in number of positive and negative feedback submissions through NEA’s public feedback portal will be compared across intervention and non-intervention clusters and across the various engagement arms.

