The surveys will be conducted in three waves, in households equally selected from the intervention and non-intervention clusters. The first survey will commence three months before and up until the beginning of *Wolbachia-Aedes* deployments. The second and third surveys will begin 3 months and 1 year following the commencement of *Wolbachia-Aedes* deployments respectively. Each survey wave will be split into three arms, (i) non-intervention clusters with no community engagement, (ii) intervention clusters with standard community engagement practices, and (iii) intervention clusters with alternate community engagement strategies. Households will be selected via stratified systematic sampling. Households will be stratified according to ethnic group denomination and minority socio-demographic factors and systemically sampled. Minority groups will be accounted for in higher proportions to reflect adequate representation of these groups. To accurately reflect the general sentiments of the working and non-working populations, surveys will be administered during the evenings of the working days and weekends. The sampled list of households across the different timepoints will be mutually exclusive to prevent contamination of questions across waves. Survey questionnaires used will be tailored to collect specific information across various timepoints and study arms. For each survey session, the surveyor will approach one respondent from each household to interview, after obtaining informed consent to participate. In the event of (i) resident refuses to participate and (ii) resident is not home, the surveyor will note down these households and arrange for a second visit, before approaching the next household on the list. In the event of a language barrier, surveyors will note the language requirements of the household and a second visit with a surveyor equipped with the necessary language skills will return to the household to conduct the survey. A maximum of one revisit to the same household will be attempted to accurately capture ground sentiments, while remaining prudent with resources.

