We also use constrained randomization to allocate clusters to receive intervention or non-intervention. This strategy, which minimizes chance imbalances in baseline characteristics between intervention and non-intervention clusters, is of greater relevance to our study since we have less study sites than the Yogyakarta study, 15 vs. 24 [39, 44]. Singapore is a densely populated city; even though the combined area of our study clusters, 10.9 km^2^, is less than half that of the Yogyakarta study, they contain roughly twice the population and more than 4.5 times the population density. A majority of Singapore’s population reside in high rise public housing apartments similar to those in the study sites. We will deploy male *Wolbachia*-*Aedes* at the ground, middle (levels 5–6), and high floors (levels 10–11) to ensure that the entire block is covered. A previous study has shown that *Ae. aegypti* can be found at all levels of apartment blocks, although lower floors tend to have more mosquitoes than higher floors [57]. We make use of a novel entomological index, the Gravitrap *aegypti* Index (GAI), for entomological surveillance. The GAI normalizes the number of female *Ae. aegypti* caught with the number of Gravitraps in the area and is currently used by the NEA for its vector control operations [57]. Besides epidemiological and entomological endpoints, we will assess the knowledge, attitudes, and acceptance of *Wolbachia*-based vector control practices of the population with two surveys conducted before and after the start of intervention. This is expected to give public health authorities insights into the social acceptability of deploying this strategy at the study sites and help educate the public on the effectiveness of this novel vector control practice.

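### Weighting of the attitude survey is triggered by differences between waves, but the need for it comes from oversampling minority groups, which can be alike in every wave

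*Protocol article*

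**What the plan says.** In the protocol article, the section on the pre-post attitudes, acceptance and knowledge survey sets the sampling rule. It describes the waves first: "The surveys will be conducted in three waves, in households equally selected from the intervention and non-intervention clusters". Strata follow: "Households will be stratified according to ethnic group denomination and minority socio-demographic factors and systemically sampled". It then adds: "Minority groups will be accounted for in higher proportions to reflect adequate representation of these groups". No wave is exempted, and no sampling fraction, sample size or population share is given. Different households are drawn in each wave.

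The statistical analysis section for the community attitudes endpoint first tests respondents' socio-demographic characteristics for differences. It then states: "If there are between-wave differences in socio-demographic characteristics, propensity score matching will be conducted and/or synthetic weights assigned to each observation", with the aim "to mirror the national level socio-demographic composition". No other weighting is stated. The comparative analysis follows: "logistic/multinomial regressions with site- and trial-specific fixed effects will be used, with socio-demographic controls added", with a site-by-trial interaction, and with odds ratios and marginal odds ratios as output.

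The Discussion gives the purpose of the surveys: "we will assess the knowledge, attitudes, and acceptance of *Wolbachia*-based vector control practices of the population". It links this to the social acceptability of the strategy at the study sites.

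**The concern.** Unequal sampling fractions create a known gap between sample and population. The sampling design opens that gap in each wave, whether or not the waves resemble each other. The plan closes it only when the waves differ from one another, which is a separate question. The more consistently the oversampling is carried out, the less likely the correction becomes.

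At stake are statements about residents as a whole: the percentage who accept the intervention, the average change from before to after release, and marginal odds ratios. Each of these averages over the mix of people in the sample. If minority and majority residents differ in attitude, or respond differently to the intervention or the engagement, the average over an oversampled mix is not the average over the population.

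**Working it through.** **Trigger against purpose.** Suppose minority groups have share P in the population and share S > P in every wave.
- The weights address the difference S − P, which is not zero.
- The trigger compares S in wave 1 with S in waves 2 and 3, a difference of zero.

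A between-wave test is then testing a true null hypothesis and fires only at its significance level. A simulation of a three-wave chi-square test (assumed 600 respondents per wave, 5% level, 4,000 runs) fired in 4.7% of runs at S = 30% and 5.1% at S = 50%. The 600 is not from the document, but the conclusion does not depend on it. When the condition is met, its and/or wording also permits matching alone. Matching can make the waves alike without restoring the national composition.

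**Effect on a level.** The plan has no figure to reproduce. All inputs here are assumptions: majority acceptance 80%, minority acceptance lower by a gap of 0 to 20 points, P of 15% or 25%, S of 30% or 50%.

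Population level = 80 − P × gap. Unweighted level = 80 − S × gap. Error = (S − P) × gap, downwards.

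| P | S | gap 0 | gap 5 | gap 10 | gap 20 |
|---|---|---|---|---|---|
| 15% | 30% | 0 | 0.75 | 1.5 | 3.0 |
| 15% | 50% | 0 | 1.75 | 3.5 | 7.0 |
| 25% | 30% | 0 | 0.25 | 0.5 | 1.0 |
| 25% | 50% | 0 | 1.25 | 2.5 | 5.0 |

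For P = 25% and a gap of 20 points, the population level is 80 − 0.25 × 20 = 75.0%. The unweighted level is 80 − 0.30 × 20 = 74.0% at S = 30% and 80 − 0.50 × 20 = 70.0% at S = 50%. Design weights restore 75.0% in both cases. The same formula gives the error in an average pre-post change if the gap is read as the between-group difference in change.

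**Effect on the interaction odds ratio.** The assumed model is: log odds = 1.0 − 0.8 × minority + 0.1 × intervention + 0.2 × post + (0.6 − d × minority) × intervention × post. It was fitted to expected values at minority shares of 25% (population) and 50% (sample).

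| Effect by group | Minority covariate | 25% share | 50% share |
|---|---|---|---|
| Equal (d = 0) | yes | 1.82 | 1.82 |
| Equal (d = 0) | no | 1.80 | 1.79 |
| Differs (d = 0.4) | yes | 1.57 | 1.42 |
| Differs (d = 0.4) | no | 1.55 | 1.40 |

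With equal effects, the adjusted odds ratio does not depend on the mix, and the unadjusted one hardly moves. With unequal effects, both move with the mix, and covariate adjustment alone does not prevent it.

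**The case against.** The strongest reply is that the planned analysis is comparative. The section specifies regressions with socio-demographic controls and does not define a population acceptance percentage as an output. If the controls include the stratifying factors, a correctly specified conditional comparison is not biased by unequal sampling of those strata. This stands, and the first row of the second table shows it. A reader might infer that the planned odds ratios are generally wrong; the documents do not support that. The reply does not cover marginal odds ratios and average changes when effects differ by group, or the aim of describing the population. The section also does not say that the controls are the stratifying factors.

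A second reply is that survey weighting is detail for the statistical analysis plan. That would answer a silent protocol. This one states a rule, and the rule's condition does not fit its purpose. The technical form of the weights can be left to the analysis plan.

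A third reply is that households differ from wave to wave, so comparability over time needs checking. This also stands. The between-wave test has a proper use and should not be removed.

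A reader might also extend the concern to feedback. Those submissions come through the public portal and not from the household sample, so oversampling does not reach them.

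**Conclusion.** The point holds in a limited form. The stated trigger cannot detect the departure from the national composition that the sampling design creates when oversampling is similar across waves. Unweighted levels, marginal odds ratios and average changes would then reflect the oversampled mix, provided that attitudes or effects differ by minority status. Without such differences the levels and average changes carry no error, and the odds ratios move little or not at all.

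It is tempting to conclude that the survey will misstate public attitudes. The documents do not support that certainty, because they give no shares, sampling fractions or attitude levels. The range of 0 to 7 points for a level, and the shift in odds ratio from 1.57 to 1.42, rest wholly on assumed inputs. The finding also takes the sentence on higher proportions to mean higher sampling fractions. If proportional allocation was intended, that sentence needs correcting instead.

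This is a secondary endpoint, and neither dengue primary endpoint is touched.

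**What to change.** In the statistical analysis section for community attitudes:

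- Apply selection-probability weights in every wave to population-level and marginal survey estimates, whatever the between-wave test shows. The weights should reflect the actual selection: stratum, equal selection from the two arms, and one respondent per household.
- Name one calibration target. The analysis section points to the national composition and the Discussion to the study sites.
- State that the stratifying factors are among the covariates in the regressions.
- Report the unweighted analysis alongside.
- Keep the between-wave test only to decide on additional adjustment for comparability between waves.

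The cost is a change of wording. Sampling fractions should be known from the design, so little or no new data collection is needed. The downside is somewhat larger standard errors from unequal weights.

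### The attitude-survey model names a site-by-trial interaction instead of an arm-by-wave term: read as 15 clusters it does not test the intervention; read as an arm flag it has no stated cluster-level error

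*Protocol article*

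**What the plan says.** The section on the community attitudes, knowledge and acceptance endpoint gives the model as "logistic/multinomial regressions with site- and trial-specific fixed effects will be used, with socio-demographic controls added". The test follows: "An interaction term between site and trial indicator variables will be added to test overall outcome differences over time between intervention and non-intervention clusters"; the same sentence extends it to engagement arms. The unit of analysis is the survey response, since weights are "synthetic weights assigned to each observation to mirror the national level socio-demographic composition". 'Trial indicator' is not defined; in context it can only sensibly mean survey wave or a before/after period.

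The survey section states that "The surveys will be conducted in three waves" and that "The sampled list of households across the different timepoints will be mutually exclusive to prevent contamination of questions across waves", so the data are repeated cross-sections. It defines the engagement arms by cluster: non-intervention clusters without engagement, intervention clusters with standard engagement, and intervention clusters with alternate engagement.

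On randomisation: "Eight out of 15 clusters were randomly selected to receive male" the releases. The Discussion uses 'site' for a cluster: "we have less study sites than the Yogyakarta study, 15 vs. 24". The mosquito endpoint section does the same. Both the case-count and the mosquito sections define a binary intervention/non-intervention group variable and interact it with a treatment-period variable. The attitude section names no such variable.

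**The concern.** The stated question is whether attitudes changed differently in intervention and non-intervention clusters, and between engagement strategies. The named term answers it on only one reading of an undefined word, and on that reading the model as stated has no term for what makes clusters move apart over time.

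Clusters can drift for local reasons such as a dengue outbreak in one estate, local publicity or a different interviewer team. A site-by-wave test counts any such drift as evidence, including drift between two non-intervention clusters. An arm-by-wave test with individual-level errors counts the chance part of the drift that falls between arms. In either case a significant result could be presented as an effect of releases or of an engagement strategy. The Discussion says the surveys should inform public health authorities about social acceptability, so the attribution matters.

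**Working it through.** The article states no sample size, power or alpha for this endpoint, so there is no figure to reproduce. The check compares null rejection rates under the two readings.

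**From the article:** 15 clusters, 8 intervention and 7 non-intervention; three waves, one before and two after releases begin; different households each wave; individual-response logistic model with site and wave fixed effects.

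**Assumed:** all 15 clusters are surveyed; *m* respondents per cluster and wave; independent cluster-by-wave drift with SD σ on the logit scale; response prevalence *p*; two-sided 5%.

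**Degrees of freedom.** Site by wave: (15 − 1) × (3 − 1) = 28. Arm by post-period: 1. Cluster-level t-test on change scores: 8 + 7 − 2 = 13.

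**Approximation.** A cluster-wave log-odds has sampling variance 1/[*m p*(1 − *p*)]. Drift adds σ², so the true variance exceeds the model's by the factor *f* = 1 + σ² *m p*(1 − *p*).
- Site by wave rejects with probability P(χ²₂₈ > 41.34/*f*).
- Arm by post with individual-level errors rejects with probability 2[1 − Φ(1.96/√*f*)].

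Example with *m* = 50, σ = 0.2, *p* = 0.5: *f* = 1 + 0.04 × 50 × 0.25 = 1.5. Site by wave: 41.34/1.5 = 27.56, giving 49%. Arm by post: 1.96/√1.5 = 1.60, giving 11%.

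**Simulation** (no intervention effect, 1000 runs per setting, prevalence about 50%):

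| *m* | σ | Site × wave, 28 df | Arm × post, individual errors | Cluster-level t, 13 df |
|---|---|---|---|---|
| 20 | 0 | 7.1% | 5.8% | 5.3% |
| 50 | 0 | 6.0% | 5.7% | 6.1% |
| 100 | 0 | 5.8% | 5.1% | 5.2% |
| 20 | 0.2 | 20.6% | 7.4% | 4.3% |
| 50 | 0.2 | 48.5% | 11.4% | 5.3% |
| 100 | 0.2 | 82.3% | 17.8% | 5.9% |
| 20 | 0.3 | 47.2% | 8.2% | 5.0% |
| 50 | 0.3 | 88.8% | 17.7% | 5.6% |
| 100 | 0.3 | 99.5% | 27.8% | 4.9% |

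The worked example agrees with its row.

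A separate three-wave simulation over *m* = 30–100 and σ = 0.15–0.3 gave 19–99% for site by wave, 7–24% for arm by post and 4–7% for the cluster-level test. The ends move by a few points with the assumptions. At *m* = 30, σ = 0.15, *p* = 0.5, *f* = 1.169 and the approximation gives 16% for site by wave. At *m* = 100, σ = 0.3, arm by post is 28% when *p* = 0.5 (*f* = 3.25) and 25% when *p* = 0.7 (*f* = 2.89).

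**Two further checks on the site-by-wave test.**
- If one non-intervention cluster shifts by 1.0 logit after baseline and nothing else changes, it rejects 14%, 24% and 52% of the time for *m* = 20, 50 and 100.
- For a real, uniform arm effect of 0.4 logit without drift, its power is 11%, 16% and 33%, against 23%, 53% and 82% for the cluster-level t-test.

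**The case against.** The strongest reply is that the sentence speaks of one interaction term and states its purpose as comparing intervention with non-intervention clusters. The same section speaks of intervention and non-intervention sites, and the two preceding sections use a binary group variable. Read with these, the term is an ordinary difference-in-differences contrast. This stands in part. The wording is ambiguous, and a reader who infers that the plan definitely tests the wrong hypothesis goes further than the article supports. The largest rejection rates belong only to the 15-cluster reading.

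Second, the section names no variance estimator, and cluster-robust errors or random effects may be in an analysis plan that is not shown. So the article does not show that clustering will be ignored. But it does state a model, with site and trial fixed effects on individual responses, and that model has no cluster-by-wave error. Robust errors would also not turn a site-by-wave term into an arm contrast.

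Third, an arm contrast built from the site terms can be estimated and has a model-based standard error. That is correct; what that standard error lacks is the between-cluster variation in change.

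Fourth, survey size and drift are assumed. That limits the size of the inflation, not its direction.

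**Conclusion.** The point holds conditionally. On the 15-cluster reading, the joint test addresses heterogeneity among clusters and is not a test of the intervention. On the arm-flag reading, the contrast is right but the stated model leaves out its error at the level of randomisation. For the assumed 30 to 100 respondents per cluster-wave and drift SD of 0.15 to 0.3, null rejection is roughly 19–99% and 7–24% respectively, against about 5% for a cluster-level test. If clusters do not drift, all are close to 5%. The same reasoning applies to the engagement arms, where the standard and alternate strategies share only eight clusters.

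This is a secondary endpoint. A reader might infer that the trial's dengue conclusions are affected; nothing here bears on the primary endpoints. The wording should be corrected before the survey data are analysed.

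**What to change.** 1. Replace the site-by-trial interaction with an explicit arm-by-wave (or arm-by-period) term, as the case-count and mosquito sections already do, and add an engagement-arm-by-wave term.
2. Define the trial indicator and say whether 'site' means a cluster.
3. Take the error from clusters. Either compute each cluster's change from the first wave (log-odds or adjusted proportion) and compare 8 with 7, by t-test or by permutation over the 3151 balanced allocations; or fit a mixed model with random cluster and cluster-by-wave effects and small-sample degrees of freedom.
4. For multinomial outcomes, apply the change scores category by category or use the mixed model.
5. Compare the two engagement strategies in the same way across the eight intervention clusters.

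This changes analysis wording only; households are sampled by cluster and wave, so no new data are needed. The cost is wider intervals, most of all for the engagement arms.
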